### **Statistical analyses**

Descriptive statistics will be obtained for all variables assessed in the study population. Mean and standard deviation will be used for normally distributed variables, mean and interquartile range for skewed distributions, proportions for categorical variables. Whenever relevant, 95% confidence intervals (95% CI) will be calculated.

Groups will be compared by means of parametric or nonparametric tests for quantitative variables (according to distribution; normality will be tested by means of the Shapiro–Wilk test) and Pearson’s  $\chi^2$  test (Fisher exact test where appropriate) for categorical variables. In all cases, two-tailed tests will be applied. P-value  $<0.05$  will be considered significant. Bonferroni correction will be used whenever relevant.

Factors potentially associated to knowledge and to patient’s satisfaction, including age, gender, comorbidities, years of education will be tested by means of univariate and multivariate quantile (median) regression models.

Stata computer software version 15 or higher (Stata Corporation, [name]) will be used for statistical analysis.

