### **Outcomes**

The main outcome will be patients' comprehension of the domains directly related to the video contents, i.e., knowledge of the *diagnosis* and its potential *complication*, corresponding to interview's questions 1-3-4 (see the attached file *Telephone Interview*).

Secondary outcomes will be the knowledge of the prescribed therapy and patients' satisfaction (see the attached file *Telephone Interview*).

The outcomes will be measured through a telephone interview, consisting of a set of questions specifically designed for the purposes of this study (see the attached file "*Telephone interview*"). The interview is made of six questions, focusing on the different domains of comprehension.

The telephone interview is conducted by one of the two researchers responsible for this task. Audio files are then stored on a computer and subsequently reexamined by both reviewers, who will assign a score to each question contained in the interview (see the attached file "*Telephone interview*").

We developed a scheme to aid the reviewers in the interpretation of patients' answers, to reduce reviewers' inter-operator variability (see the attached file *Interpretation of patients' answers*).

Patients' answers will receive a score on a 4-point Likert scale (ranging from zero to three) from low to high knowledge.

Scores from the two independent reviewers will be summed to obtain an overall score. The score for the main outcomes will therefore range: 0-18 for the main outcome (questions 1-3-4), 0-6 for the knowledge of the prescribed therapy (question 2), 0-12 for patient's satisfaction (questions 5-6).

To the best of our knowledge, no currently available validated questionnaires would serve for the purpose of our study, i.e., for the simultaneous measurement of different domains of comprehension across two different medical conditions.

Hence, we have developed the ad-hoc interview and its related interpretation scheme using face and content validity. Construct validation would require an amount of time and resources equivalent to that of the trial itself, pushing it beyond practical feasibility.

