In this second version of the protocol, we added two safety outcomes. The first is patient adherence to anticoagulation prescribed at hospital discharge. The second outcome is incidence of the main complication (stroke/pulmonary embolism) at a median follow up. This amendment is felt necessary due to relatively frequent patient-reported non-adherence to anticoagulants observed during telephone interviews.

Data for adherence rate to anticoagulants will be obtained from an additional review of the audio recording of the interview. This will be performed by one of the two reviewers.

Incidence of complications at median follow up will be assessed via a second telephone contact with recruited participants (patients or caregiver), using the same contact information provided at the time of recruitment. We will make a maximum of five attempts of contact, after which participants will be considered lost at follow up.

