## **Sample size**

We hypothesize a median score for the primary outcome to be 10 points in the control group, whereas we expect a 20% higher score in the intervention group as suggested by current literature, with standard deviation 4 and non-normal distribution. Group sample sizes of 64 and 64 achieve 80% power to detect this difference with alpha error 5% using a two-sided Mann-Whitney test assuming that the actual distribution is uniform. (Note: this number represents the total number of patients with either DVT or AF, within each study group, since we do not expect differences in the effect by diagnosis).

Since we expect the number of patients lost to follow-up to be 10%, we plan to enroll 72 patients in each group (144 patients in total).

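### Plain Bonferroni, with its scope left open, is a needlessly weak multiplicity rule: the single primary needs no correction, and Holm would serve the two secondary scores better at no cost (minor)

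*Protocol*

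**What the plan says.** Statistical analyses in the Protocol sets a threshold of p<0.05 and states "In all cases, two-tailed tests will be applied". Directly after the threshold it adds: "Bonferroni correction will be used whenever relevant". No other multiplicity rule appears in the Protocol, and this one gives no family, trigger or divisor.

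Outcomes defines one main score (0-18, questions 1, 3 and 4). It continues: "Secondary outcomes will be the knowledge of the prescribed therapy" (0-6) and patient satisfaction (0-12). For the second version of the Protocol it reports that "we added two safety outcomes": adherence to anticoagulation and incidence of the main complication. Statistical analyses also plans quantile regressions on several factors.

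Sample size puts the whole 5% on the main score: "Group sample sizes of 64 and 64 achieve 80% power to detect this difference with alpha error 5% using a two-sided Mann-Whitney test".

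Statistical methods says that a full statistical analysis plan was approved before the study began, that it is signed before any analysis, and that changes made after database lock will be reported.

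**The concern.** The rule names a method but not its scope. Two analysts working from the Protocol alone could apply it differently. One might divide 5% across the three interview scores, which would test the primary at a stricter level than the one that determined the sample size. Another might decide that no correction is relevant and test each secondary score at 5%, which leaves their joint error rate uncontrolled.

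There is also a point that does not depend on scope. Wherever a correction is made, Bonferroni gives up power that Holm's step-down procedure keeps under the same error guarantee and with no further assumptions. What is at stake is power for therapy knowledge and satisfaction, and agreement between the primary test and its stated power.

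**Working it through.** **Inputs.** From Sample size: control score 10, difference 20% of 10 = 2 points, SD 4, so standardised effect d = 2/4 = 0.5; 64 analysed per arm; two-sided alpha 5%; 10% loss. From Outcomes: one primary score, two secondary scores, two safety outcomes. For secondary power I assume d = 0.5, because the Protocol gives no secondary effect size.

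**1. The plan's own figure.** Normal approximation: n = 2(1.960 + 0.842)²/0.5² = 62.8, so 63 per arm. The exact t calculation gives 64 per arm and 80.15% power. Allowing for loss: 64/0.90 = 71.1, so 72 enrolled. The stated 64 and 72 reproduce. For a uniform distribution the Mann-Whitney test has asymptotic relative efficiency 1 against the t-test, so I use the t calculation throughout.

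**2. Primary placed in a Bonferroni family of k tests.** Alpha = 0.05/k, noncentrality = 0.5 × √(64/2) = 2.83, 126 degrees of freedom:

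| Family | Alpha | Power at 64 per arm | Analysed per arm for 80% |
|---|---|---|---|
| Primary alone | 0.05 | 80.1% | 64 |
| k = 2 | 0.025 | 71.2% | 78 |
| k = 3 (primary and two secondary scores) | 0.0167 | 65.6% | 86 |
| k = 5 (adding two safety outcomes) | 0.01 | 58.5% | 96 |

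The last three requirements all exceed the 72 enrolled per arm.

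**3. Secondary scores left uncorrected.** Chance of at least one false positive in two independent tests: 1 − 0.95² = 9.75%. With Bonferroni at 0.025 each: 1 − 0.975² = 4.9%. Positive correlation between the scores would lower the 9.75%.

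**4. Bonferroni against Holm for the two secondary scores.** Bonferroni tests each at 2.5%, so power for each is 71.2%. Holm tests the smaller p-value at 2.5% and, if that is rejected, the other at 5%. A given score is therefore rejected if its own p ≤ 0.025, or if its p lies between 0.025 and 0.05 and the other score's p ≤ 0.025. With independent tests:

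0.712 + (0.801 − 0.712) × 0.712 = 0.712 + 0.063 = 0.775, or 77.6% with unrounded inputs.

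The normal approximation gives 72.1% against 78.3%. Familywise error is at most 5% under both methods, whatever the correlation.

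**5. The results attached to the Protocol.** In Secondary Analyses, the unadjusted p-values for primary score, therapy knowledge and satisfaction are 0.0001, 0.36 and 0.17, in both the per-protocol and the sensitivity tables. Multiplying by 3 or 5 leaves the first far below 0.05; the other two are above it already. The main intention-to-treat result is not shown. Adding zero scores for the missing patients (3 standard, 4 video) to the published summaries and running t-tests gives p = 0.0004, 0.48 and 0.30, with the same conclusion.

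**The case against.** The strongest reply is that the make-up of a multiplicity family is ordinarily left to the statistical analysis plan, and Statistical methods says that such a plan was approved before the study started. That stands. A reader might infer that the wording lets the family be picked once results are known. The documents do not show this: the plan is unseen and may define the family, and changes after database lock are to be reported. The open scope is therefore not a finding in itself.

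A second reply is that nothing puts the primary in a corrected family. That also stands. With one main score sized at an undivided 5%, a reader who infers that the plan lowers the primary's power goes further than the text. The 66% and 59% figures describe a permitted reading, not the natural one. Likewise, a false-positive rate over all five outcomes (1 − 0.95⁵ = 22.6%) would count the primary, which is entitled to its own 5%. Over the other four it is 1 − 0.95⁴ = 18.5%, and two of those are labelled safety outcomes.

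A third reply is that Bonferroni is valid, the secondary aims are worded cautiously in Objectives, and preferring Holm is a matter of taste. Bonferroni is indeed valid, and each test does have a defined 5% level; only the joint rate is open. But Holm is not merely an alternative style. It rejects everything that Bonferroni rejects and sometimes more, under the same guarantee, and it needs no extra patients or data. That part of the point remains.

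**Conclusion.** The point holds in a limited form and is minor. The Protocol names plain Bonferroni as its only multiplicity method and leaves its scope open. Read naturally, the primary is tested alone at two-sided 5% and keeps its 80% power; saying so would rule out the reading that takes it to about 66%. Leaving the two secondary scores uncorrected would give about 9.75% familywise error if they are independent, and somewhat less if, as is likely for answers from one interview, they are positively correlated. Where correction is made, Bonferroni costs about 6 percentage points of power per secondary score compared with Holm. That figure assumes independent tests, a 0.5 SD effect on both scores and 64 per arm; the direction of the advantage needs none of these assumptions. In the per-protocol and sensitivity results shown, the choice changes no verdict.

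**What to change.** Replace the Bonferroni sentence in Statistical analyses with: *The primary score is tested alone at two-sided 5% without correction. The two secondary scores (therapy knowledge, satisfaction) are tested with Holm's procedure at an overall two-sided 5%. Safety outcomes and factor models are outside this family and are reported as estimates with 95% confidence intervals.* The statistical analysis plan should carry the same wording.

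Testing the secondary scores only after a significant primary is optional. Its small downside is that no confirmatory secondary claim is possible if the primary fails.

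The cost is one sentence. Sample size, data collection and the primary analysis are unchanged.

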## Objectives

The aim of this study is to assess the utility of two interventional videos, shown to patients discharged from the ED with a diagnosis of atrial fibrillation or deep vein thrombosis. We have focused our attention on these two medical conditions because they share some important features: they are frequently seen in EDs; their main complication (stroke and pulmonary embolism) can cause significant morbidity and mortality; both conditions and their related complications are probably not

very intuitive to comprehend for the general population. In fact, the understanding of these conditions implies the knowledge of a number of pathological processes, with which most people are unfamiliar.

The primary hypothesis is that patients enrolled in the study group will show a higher degree of comprehension of their medical condition and its related complications, as compared to the control group. Secondly, we will also analyze any possible effect of the videos on the knowledge of the therapy prescribed, return instructions and patients' satisfaction with the quality of communication in the ED.

Eventually, we will examine the association of some factors with the outcomes (age, sex, level of education, atrial fibrillation vs. deep vein thrombosis group).

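### The arm comparison is unadjusted although age and education are collected: a modest, avoidable loss of precision, not a bias

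*Protocol*

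**What the plan says.** For the arm comparison, the Statistical analyses section states: "Groups will be compared by means of parametric or nonparametric tests for quantitative variables". The choice follows a Shapiro–Wilk test, and no covariate is mentioned. The Sample size section rests on the same kind of comparison: "alpha error 5% using a two-sided Mann-Whitney test assuming that the actual distribution is uniform".

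Patient characteristics appear in a separate sentence of Statistical analyses. Factors that may be associated with knowledge and satisfaction, "including age, gender, comorbidities, years of education will be tested by means of univariate and multivariate quantile (median) regression models". The arm is not among the named terms. The Objectives section gives the purpose: "Eventually, we will examine the association of some factors with the outcomes (age, sex, level of education, atrial fibrillation vs. deep vein thrombosis group".

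Four other places bear on the point:
- Background and rationale lists differences in education and demographics among the things that make communication harder.
- Eligibility criteria sets no limit on education or comorbidity.
- Analysis strategy gives patients lost to follow-up a score of zero in the main analysis.
- Years of education appears on the Telephone Interview form (Supplementary Data 3) as four categories.

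The per-protocol and sensitivity results in Supplementary Data 5 are unadjusted two-sample t tests. The protocol nowhere describes an adjusted arm effect.

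**The concern.** The protocol gives a reason to think education and demographic factors bear on comprehension, and it plans to study them, but it keeps them out of the comparison the trial exists to make. Allocation is stratified by centre only, so age and education are balanced between arms by chance alone. Any score variance they explain stays in the error of the video effect, and a chance imbalance moves the estimate. Adjusting for baseline predictors would narrow the interval at almost no cost.

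A smaller matter runs the other way. If the arm is left out of the factor model, the video effect becomes noise in the age and education estimates.

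**Working it through.** **Inputs from the Sample size section.** Control score 10: "We hypothesize a median score for the primary outcome to be 10 points in the control group". Effect: "whereas we expect a 20% higher score in the intervention group", so 0.20 × 10 = 2 points. Spread: "with standard deviation 4 and non-normal distribution". Size and power: "Group sample sizes of 64 and 64 achieve 80% power to detect this difference". Expected loss is 10%, and planned enrolment is 72 per arm.

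**Assumed input.** R², the share of score variance among patients reached that age and education explain together. The protocol gives no value, so a range of 0.05 to 0.30 is shown.

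**1. The plan's own figure.** The two-sided 5% t-test solution for difference 2 and SD 4 is 63.8, so 64 per arm, with power 80.1%. Then 64/0.9 = 71.1, so 72. Both stated numbers reproduce.

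**2. Patients reached, 64 per arm.** Residual SD = 4 × √(1 − R²), SE = residual SD × √(2/64), equivalent unadjusted n = 64/(1 − R²).

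| R² | Residual SD | SE | Power | Equivalent n per arm |
|---|---|---|---|---|
| 0 | 4.00 | 0.707 | 80.1% | 64 |
| 0.05 | 3.90 | 0.689 | 82.1% | 67 |
| 0.10 | 3.79 | 0.671 | 84.1% | 71 |
| 0.20 | 3.58 | 0.632 | 88.1% | 80 |
| 0.30 | 3.35 | 0.592 | 91.8% | 91 |

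On the appended per-protocol table (pooled SD 3.73, SE 0.637), the 95% half-width of 1.26 would become 1.23, 1.19, 1.13 or 1.05 at R² of 0.05, 0.10, 0.20 or 0.30.

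**3. Main analysis with zeros, 72 per arm.** Assume 10% lost in each arm, unrelated to the covariates.
- Means: 0.9 × 10 = 9.0 and 0.9 × 12 = 10.8, so the difference is 1.8.
- Variances: 0.9 × (16 + 100) − 9.0² = 23.40 and 0.9 × (16 + 144) − 10.8² = 27.36. The average is 25.38, so SD 5.04.
- Variance the covariates can remove: 0.9² × 16 × R² = 12.96 × R².

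| R² in patients reached | Share of main-analysis variance | Residual SD | Power |
|---|---|---|---|
| 0 | 0% | 5.04 | 57% |
| 0.10 | 1.30/25.38 = 5% | 4.91 | 59% |
| 0.20 | 2.59/25.38 = 10% | 4.77 | 61% |
| 0.30 | 3.89/25.38 = 15% | 4.64 | 64% |

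The zeros add variance that age and education cannot explain, so the gain is about 2 to 7 points instead of 4 to 12.

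**4. Education and missing values.** If education is obtained only at the telephone call, a patient not reached has both missing education and a score of zero. A missing-education category then identifies the lost patients and absorbs their zeros. A simulation used 72 per arm, a true effect of 2 in patients reached, and assumed losses of 5% (control) and 15% (video). The expected zero-scored difference is 0.85 × 12 − 0.95 × 10 = 0.70.

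| Estimate | Arm difference |
|---|---|
| Zero-scored, unadjusted | about 0.7 |
| Zero-scored, adjusted for age only | about 0.7 |
| Zero-scored, adjusted with missing-education category | about 1.85 |
| On-treatment | about 2.0 |

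Age adjustment leaves the planned estimate where it is. The missing category moves it almost to the on-treatment value.

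**5. Arm omitted from the factor model.** In a linear model with 1:1 allocation, a 2-point effect adds (2/2)² = 1 to the variance, and √(17/16) = 1.03, so factor standard errors are about 3% wider. On the appended table, 3.94/3.73 = 1.06. The plan specifies median regression, which this ratio does not govern, so these are rough guides.

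**The case against.** The strongest reply is that nothing here is wrong. An unadjusted comparison in a randomised trial is valid, and the sample size was set on one. The protocol refers to a full SAP that is not shown, and its factor list is open-ended. That list also leaves out diagnosis, which Objectives promises to examine, so it looks illustrative. No explained variance is given, and at R² = 0.05 the gain among patients reached is only 2 power points.

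Most of this stands, and it rules out several stronger readings:
- A reader might infer that the unadjusted result is biased. It is not.
- A reader might infer that the arm is excluded from the factor model. The text shows only that it is not named.
- A reader might take age and education to be established predictors. Objectives and Statistical analyses treat them as candidates to examine, and the support in Background and rationale is general.
- A reader might apply the rise from 80% to as much as 92% to the main analysis. With lost patients scored zero, that does not follow.

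What the reply does not remove is that the protocol itself fixes the form of the arm comparison and gives the covariates a different role. This is a choice already made, not a detail left to the SAP. Even with the arm added, the factor model would estimate a median difference and not an adjusted version of the mean differences in Supplementary Data 5.

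**Conclusion.** The point holds as a loss of efficiency: worth changing, but not a threat to validity. Among patients reached, power rises from 80% to about 82% to 92% for an assumed R² of 0.05 to 0.30. In the zero-scored main analysis it rises from about 57% to 59% to 64% for an assumed 0.10 to 0.30, with 10% lost in each arm and loss unrelated to the covariates. These gains are for age and education together; age alone gives only its own share.

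**What to change.** - Report a linear model with robust standard errors for the primary score, with terms for arm and baseline age. Keep the Analysis strategy handling of lost patients, and show the unadjusted comparison alongside.
- Add years of education only if it is recorded before randomisation, or if missing values are filled by a single imputation blind to arm and outcome. Do not use a missing-category indicator.
- State whose age and education count when a caregiver is the participant.
- Name the arm as a term in the factor model.
- Because results are already appended, label any adjusted estimate added now as supportive, and describe it as a change in the clinical study report, as Statistical methods requires for changes after database lock.

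The cost is one regression, a few lines of text and a rule for missing education. The downside is that two estimates of the video effect have to be reported.

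### Median regression suits the factor analyses poorly: it is unreliable on the 0-6 therapy score and loses power on the 0-18 main score

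*Protocol*

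**What the plan says.** The Objectives section of the Protocol ends by stating that "we will examine the association of some factors with the outcomes". The Statistical analyses section names the variables and outcomes ("Factors potentially associated to knowledge and to patient’s satisfaction, including age, gender, comorbidities, years of education") and fixes the method as "univariate and multivariate quantile (median) regression models". It attaches no condition to that choice, whereas the group comparisons in the same section choose between parametric and nonparametric tests according to distribution.

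The Outcomes section defines the scores. Each item is graded in four steps: "Patients' answers will receive a score on a 4-point Likert scale (ranging from zero to three) from low to high knowledge". Then "Scores from the two independent reviewers will be summed to obtain an overall score". The resulting ranges are "0-18 for the main outcome (questions 1-3-4), 0-6 for the knowledge of the prescribed therapy (question 2"), and 0-12 for satisfaction (questions 5 and 6). Under Analysis strategy, the main analysis gives patients lost to follow-up a score of zero.

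**The concern.** Inference for a median regression coefficient normally rests on the outcome having a smooth density at the median. A sum of a few 0-3 ratings has point masses instead. The two reviewers grade the same recording against a shared scheme meant to reduce disagreement, so even totals dominate whenever they agree. The fitted median then tends to sit on one score value or jump to another, and the standard error has no firm basis.

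At stake is the stated objective of finding which patient factors go with comprehension and satisfaction. With an unreliable test, factors with no effect may be reported as associated with therapy knowledge, and real associations may be missed.

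**Working it through.** **1. The plan's own figure.** Inputs from Sample size: control 10 points, 20% higher with video (difference 2), SD 4, two-sided alpha 5%, power 80%.

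- n per group = 2 × (1.96 + 0.842)² × 4² / 2² = 62.8, so 63. The t-test version gives 63.8, so 64.
- The efficiency of Mann-Whitney relative to the t test is 1.0 under a uniform distribution, so 64 stands. Then 64 / 0.90 = 71.1, so 72 per group and 144 in total.

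The figure is reproduced. It concerns the arm comparison and is not in dispute here.

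**2. Median against mean on the same inputs.** For an evenly split factor with that effect, z = 2 / (4 × √(2/64)) = 2.83.

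- Mean: Φ(2.83 − 1.96) = 0.81.
- Median, normal distribution (efficiency 0.637): Φ(2.83 × √0.637 − 1.96) = Φ(0.30) = 0.62.
- Median, uniform distribution (efficiency 0.333, the plan's own distributional assumption): Φ(2.83 × √0.333 − 1.96) = Φ(−0.33) = 0.37.

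This ignores ties and shows only the direction of the loss.

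**3. How coarse the 0-6 score is.** It has 7 possible values, so 144 patients average 144 / 7 ≈ 21 per value. Under perfect reviewer agreement only 0, 2, 4 and 6 occur, or 144 / 4 = 36 per value. The appended tables show 137 of 144 reached, so the main analysis adds 7 zeros. The large-sample standard error of a median is 1 / (2 f √n), with f the density at the median. At a point mass f does not exist, and its estimate depends on the bandwidth. For a binary factor alone, the coefficient is simply the difference of two group medians, so it is often exactly zero.

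**4. Simulations.** Taken from the appended tables: n = 137; therapy score mean 3.26, SD 1.79; main score mean 7.45, SD 3.94. Assumed: item distributions, reviewer agreement (60-100%), size of the factor effect, and standard-error method. The iid method below assumes identically distributed errors.

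*0-6 score, no true effect, nominal 5%:*

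| Setting | Median regression | Comparator |
|---|---|---|
| Set A, iid, all item distributions | 0-52% | linear or rank 2.5-7% |
| Set A, two distributions matched to the appended mean and SD | binary factor alone 24-52%; age 7-25%; one factor in a multivariable model 11-19% | as above |
| Set A, another distribution (mean 3.3, SD 1.85) | 1.5-30.5% | as above |
| Set A, median well inside one mass point | 0-2%; standard error exactly zero in up to 89% of datasets | as above |
| Set B, iid, 80% agreement (mean 3.25, SD 1.85) | univariate 35-48%; multivariable 23-24% | robust linear 4-9%; proportional odds 5-8% |
| Set B, bootstrap | 4-8% | as above |

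Set A used 400 runs per cell for iid standard errors. Adding the 7 zeros gave 48% and 54% in the two cells tried. A further bootstrap check in Set A, for a binary factor alone (600 runs per cell), gave 0-13%, with a zero standard error in up to 81% of datasets. A separate bootstrap check of a model with four null covariates gave 2.2-4.4% in one distribution and 2.8-3.5% in another, with no zero standard errors. That check had about 140 runs per cell, so its Monte Carlo margin is 1.96 × √(0.05 × 0.95 / 140) = 3.6 points.

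*0-6 score, true shift:* in Set B, bootstrap median regression detected 8% against 54% for linear regression, and about half the coefficients were exactly zero. In Set A the iid version detected 34-58% against 72-78%, but those figures are not power at 5% because the test does not hold its level.

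*0-18 score:* false positives were 5% in Set B. In Set A they were 3-10% in most cells, with 25% for a binary factor alone under perfect agreement. Power was 64% against 82% in Set B. In Set A it was 62-72% against 84-93% (43-65% with bootstrap).

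*0-12 score, Set A, perfect agreement:* false positives were 13% for a binary factor alone and 8.5% in a multivariable model.

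**The case against.** The strongest reply is that the Protocol names a model and not a standard-error method. The latter belongs in the SAP, which is not shown. A reader might infer that the p-values for the 0-6 score are invalid in every case and always too small. The documents do not support that. The false-positive rate depends on the standard-error method, on where the median falls and on reviewer agreement, and the Protocol fixes none of these. Some settings are near nominal or conservative, and bootstrap standard errors largely restore the level in multivariable models. This part of the reply stands.

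It does not rescue the choice, because the bootstrap version has very little power on this score. The model does poorly under either method: with iid errors the level is not held, and with bootstrap errors the factor is rarely detected.

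A second reply is that the Sample size section speaks of a median and a non-normal distribution, so median regression is coherent with the design, and no power target is set for factors. For the 0-18 score this largely holds: the issue there is efficiency, not error rate.

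A reader might also extend the point to the treatment effect. The plan assigns median regression to no arm comparison, adjusted or unadjusted. Arms are compared by parametric or nonparametric tests, and the sample size uses Mann-Whitney ("Group sample sizes of 64 and 64 achieve 80% power to detect this difference with alpha error 5% using a two-sided Mann-Whitney test").

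**Conclusion.** The concern holds for the secondary factor analyses. On the 0-6 therapy score, median regression is unreliable: about 0% to 50% false positives with iid standard errors (23-48% in Set B), or a level near 5% with about 8% power against 54% under the bootstrap. On the 0-18 score the level is mostly near nominal and the cost is power, about 64% against 82%. The 0-12 score shows some inflation in the two settings tried.

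These sizes rest on assumed item distributions, assumed reviewer agreement (80% in Set B) and assumed effects. Matching the appended mean and SD does not settle the rate, as the spread in Set A shows. What does not depend on those assumptions is that the outcomes are coarse and tied by construction. The primary arm comparison and the sample size are untouched, so this is a change that should be made, not one on which the trial's main conclusion depends.

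**What to change.** In Statistical analyses, replace quantile (median) regression for the knowledge and satisfaction scores by proportional-odds ordinal logistic regression, or by linear regression with robust standard errors. Name one of the two as the method, for both the univariate and the multivariable models.

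The cost is one sentence; both are standard commands in the software the Protocol names. The downside is that effects become odds ratios or mean differences and no longer differences in medians. If proportional odds is chosen, its assumption should be checked, in particular with lost patients scored zero, a setting in which that model was not simulated here. If the database is already locked, the Protocol's own rule applies: describe the change in the clinical study report.
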